### Blinding

Since the occupational health care professionals can be involved in guidance of participants of both the intervention group and the usual care group and because the new RTW program contains several new elements compared to usual care, i.e. a combined consult with the insurance physician and the labour expert, meetings with the RTW coordinator, and contracting of a vocational rehabilitation agency for finding a temporary (therapeutic) workplace, the occupational health care professionals cannot be blinded for the allocation. Furthermore, most outcome measures are self-reported, which also makes blinding for the participants not possible. However, the occupational health care professionals and RTW coordinators are not involved in the assessment of the outcomes. Moreover, since all follow-up questionnaires are sent to the participants by postal mail, it is unlikely that direct influence of the researchers or occupational health care professionals will occur.

Since the registration of sickness benefit is done by the SSA, these measurements can be derived from the computerised SSA database. Therefore, bias due to a lack of blinding is prevented for this outcome. Blinding for the secondary outcomes is not possible, because these measurements are derived from self-reported data. After randomisation all participants receive a research code consisting of a unique consecutive number. All data will be put in the computer by a research assistant, using this research code, to guarantee that analyses of the data by the researcher will be blinded.

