### Outcomes

#### Effect evaluation

The primary outcome measure in this study is: duration of the sickness benefit period from the first day of reporting sick until ending of the sickness benefit. Recurrence of sickness absence with an accepted sickness benefit claim within 4 weeks after ending of the previous sickness benefit is considered as belonging to the preceding sickness benefit period, on condition that it is due to the same (or related) MSD. Also, for calculation of the total duration of sickness benefit during the one-year follow-up awarded sickness benefit claims are only included when due to same (or related) MSD.

Secondary outcome measures are:

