#### - RTW

When measuring the effect of a RTW intervention, it can be expected to take actual RTW as an important outcome measure. For sick-listed employees full RTW and ending of the sickness absence period coincides, in principle. However, for the sick-listed temporary agency worker and the sick-listed unemployed worker moving from being sick-listed to end of sickness benefit does not automatically also mean full RTW. Because in most cases these workers have no workplace/employer to return to, the worker can report being fully recovered from illness or the insurance physician of the SSA can establish full recovery of functional limitations (assessed with regard to last/previous work) without actual RTW of the worker. Therefore, RTW is measured as a separate outcome measure. RTW is defined as: duration from the first day of reporting sick until actual first RTW in any type of paid work or work resumption with ongoing benefits. Since for the majority of these workers there is no workplace to return to, working in the same or different type of work(place) is classified as RTW.

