#### Effect evaluation

In this study survival analysis will be used to analyse sickness benefit data with regard to the first period of sickness benefit. To describe the duration until ending of sickness benefit in both groups, the Kaplan Meier method will be used. In order to calculate hazard ratios the Cox proportional hazard model will be applied. If necessary, standard errors will be corrected for clustering. Differences in total days of sickness benefit during the one-year follow-up will be analysed with a general linear model. If necessary, the results will be adjusted for dissimilarities at baseline. Longitudinal random coefficient analyses will be used to assess differences in secondary outcome measures. Finally, intraclass correlation coefficients will be calculated at the level of the insurance physician, since the insurance physician plays a key role in acceptance of the sickness benefit claim and the assessment of (sufficient) recovery of functional limitations, i.e work ability, with ending of the sickness benefit.

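### The protocol says lack of blinding cannot bias the primary outcome, but the decision that ends the benefit is made by an unblinded physician or an unblinded worker

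*Protocol article*

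**What the plan says.** The protocol article defines the primary outcome (Outcomes, Effect evaluation) as "duration of the sickness benefit period from the first day of reporting sick until ending of the sickness benefit".

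The Blinding section makes four statements that bear on it:

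- On the staff: "the occupational health care professionals cannot be blinded for the allocation".
- On their role in measurement: "the occupational health care professionals and RTW coordinators are not involved in the assessment of the outcomes".
- On the data source: "Since the registration of sickness benefit is done by the SSA, these measurements can be derived from the computerised SSA database".
- The conclusion drawn from that source: "Therefore, bias due to a lack of blinding is prevented for this outcome".

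Elsewhere the article says who brings the primary event about. The RTW subsection of Outcomes explains that benefit can stop without any return to work, because the worker may report recovery or because "the insurance physician of the SSA can establish full recovery of functional limitations". Under Statistical analyses, Effect evaluation, the reason for computing intraclass correlations by physician is that "the insurance physician plays a key role in acceptance of the sickness benefit claim and the assessment of (sufficient) recovery of functional limitations". That sentence goes on to link the recovery assessment to the benefit ending. The Sample size section uses the same reason to inflate for clustering.

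Limitations of the study acknowledges, in general terms, that workers and professionals are not blinded. It does not mention the primary outcome and does not withdraw the statement in the Blinding section.

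**The concern.** The Blinding section treats two things as one: how the end date is captured and how the end date comes about. Taking a date from an administrative system removes reporting and transcription error. It does not blind the judgement that put the date there. In the Cox model the event is the ending of the benefit, so that judgement is the event.

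The physician who makes this judgement is also close to the intervention. Insurance physicians are trained in the program and sit on the program teams (Training of the OHC professionals). They give the intervention group its home assignment and write to the general practitioner (Combined consult). They may also handle control participants (Contamination). They therefore know the arm and hold program information on one arm only.

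At stake is how the primary result may be interpreted. A reader who accepts the sentence will treat a hazard ratio on benefit duration as free of bias from lack of blinding. The design does not give that assurance.

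**Working it through.** **1. The statements side by side**

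| Question | Blinding section | Other sections |
|---|---|---|
| Do professionals take part in determining the outcome? | No | Yes: the physician's recovery assessment is tied to the benefit ending (Effect evaluation under Statistical analyses; Sample size; RTW) |
| Do those who can end the benefit know the allocation? | Professionals and participants cannot be blinded | Limitations confirms this for both; the worker opens the allocation envelope (Randomisation procedure) |
| What does the database protect? | All bias from lack of blinding | Only registration of the date is described (Data collection; Strengths) |

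The RTW subsection names two routes to the end of benefit, worker report and physician decision. Neither is blinded. The statement that bias is prevented therefore does not follow from its premise.

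**2. The plan's own arithmetic relies on the physician's influence**

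Inputs from Sample size: hazard ratio 2.0, two-sided alpha 0.05, power 0.80, 1:1 allocation, two thirds with an event, 10% loss, ICC 0.05, 10 clusters.

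- Events (Schoenfeld): (1.960 + 0.842)² / (0.25 × (ln 2)²) = 65.3, so 66.
- Participants: 66 / (2/3) = 99, against the stated 100.
- Loss: 100 × 1.1 = 110, as stated.
- Clustering: with 100/10 = 10 per physician, the design effect is 1 + (10 − 1) × 0.05 = 1.45, and 110 × 1.45 = 159.5, so 160, as stated.

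The figures reproduce and are not in dispute. The last step matters here: 50 extra participants are enrolled because outcomes are expected to depend on which physician assesses the worker. That does not fit with the same professionals having no part in outcome assessment.

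**3. Sensitivity, for illustration only**

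The documents give no size for any bias, so the spurious hazard ratios below are assumptions. Suppose there is no true effect and unblinded decisions alone produce the hazard ratio h. With d events and 1:1 allocation, the test statistic is shifted by δ = √(d/4) × ln h, and the chance of two-sided p < 0.05 is 1 − Φ(1.96 − δ) + Φ(−1.96 − δ).

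Two values of d are used: 160 × 2/3 ≈ 107, and 107 / 1.45 ≈ 74 after allowing for clustering.

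| Assumed spurious h | d ≈ 107 | d ≈ 74 |
|---|---|---|
| 1.0 | 5% | 5% |
| 1.1 | 8% | 7% |
| 1.2 | 16% | 12% |
| 1.3 | 27% | 20% |
| 1.5 | 56% | 41% |

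For example, h = 1.2 and d = 107 give δ = √26.75 × 0.182 = 0.94 and a rejection probability of about 16%. The two-sided figures are the same for 1/h, that is, for bias against the program.

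**The case against.** The best defence has three parts, and each has some force.

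- **Blinding is impossible here, and the article says so.** Limitations of the study lists it first. This stands, and nobody should ask for blinding. But the general admission leaves the specific assurance about the primary outcome in place, and Strengths of the study presents the agency's registration as reliable.
- **Registry data do protect the outcome.** They guard against recording, recall and attrition bias, and the article also describes coded data entry and blinded analysis. A reader might infer that the primary outcome has no protection at all; the documents do not support that. The protection is real but narrower than claimed.
- **A physician acting on the plan may be part of the program.** The plan report goes to the physician (Preparation of implementation), who takes over further guidance (Evaluation), in a trial described as pragmatic. Earlier closure for a worker with a plan could thus be a genuine effect. Likewise, benefit that continues during a temporary placement is a designed feature (Placement in a matching workplace) and is not evidence of biased judgement. This stands, and it is one reason why the direction of any bias cannot be stated.

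Two further inferences are tempting and should not be drawn. The first concerns recurrences, which count towards the same period "on condition that it is due to the same (or related) MSD". One might suppose that the treating professionals' diagnosis codes decide this, but the article does not say who judges relatedness or whether that person is blinded. The second is that an all-cause analysis should have to agree before the trial may conclude anything. That would add a hurdle without addressing blinding, and it would bring unrelated illness into a musculoskeletal trial.

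**Conclusion.** The concern holds as an internal contradiction. The Blinding section claims a property that the RTW, Sample size and Effect evaluation sections show the design does not have. The unblinded physician also has program tasks, although the program's three main stakeholders are the worker, the labour expert and the RTW coordinator. It would overstate the point to describe the physician as its main deliverer.

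The documents do not give the size of any bias, its direction, or the split between worker-ended and physician-ended benefit. The false-positive figures above rest on assumed spurious hazard ratios and show only that a modest bias would matter at this sample size. They do not show that the trial is biased.

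The correction is worth making because it changes what may be claimed for the primary endpoint. It does not threaten the trial's feasibility or its sample size.

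**What to change.** 1. In Blinding, restrict both sentences to the recording of the outcome: database extraction limits bias in how the end date is registered and retrieved, and the professionals do not collect the outcome data. Remove the claim that bias from lack of blinding is prevented.
2. In Limitations of the study, extend the existing statement to the primary event: the decision to end benefit is taken by a physician or reported by a worker who knows the allocation, and bias of unknown size and direction is possible.
3. Data collection already provides for checking benefit data against the medical file. Where that file shows it, record whether the worker or the physician ended the benefit, and report the counts by arm as a descriptive sensitivity analysis. It should not be presented as a test that isolates bias: both routes are unblinded, and the route is determined after randomisation and may itself be changed by the program.

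The cost is two text changes, a slightly less favourable claim for the primary endpoint, and one extra field. The article does not say that the files always hold this information, so some values may be missing and should be reported as unknown.

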### Co-interventions and compliance

Unfortunately, in this pragmatic RCT it is not possible to avoid co-interventions during the intervention period, because asking the temporary agency workers, the unemployed workers, and the occupational health care professionals of the SSA to stop or not start with other treatments will lead to less participation. To measure the compliance with the new RTW program, the participants, the occupational health care professionals, the RTW coordinators, and the case-managers of the vocational rehabilitation agencies are asked independently about all interventions applied. Also, both the intervention group and the control group are asked about co-interventions in each follow-up questionnaire. If necessary, we can adjust for co-interventions in the multivariate analysis.

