#### - Direct and indirect costs

Direct costs are paid by the SSA for interventions regarding vocational rehabilitation support, e.g. training/education, for interventions aimed at health promotion, e.g. physical therapy (graded activity) and/or psychological help, or interventions aimed at RTW, e.g. searching for a (temporary) workplace by contracting a vocational rehabilitation agency or temporary placement in work with a willing employer and with an ongoing benefit. Information regarding direct costs is collected from the SSA database and the worker's files after one year of follow-up.

Indirect costs are related to costs due to paid sickness benefit for the sick-listed workers with MSD. When looking at sick-listed temporary agency workers and sick-listed unemployed workers, loss of productivity is not part of the indirect costs. When reporting sick the temporary agency workers immediately falls under the SSA for substituted income, i.e. the sickness benefit. The temporary agency replaces the sick-listed temporary agency worker with a healthy worker at the company/workplace concerned with no productivity loss as a result. Therefore, indirect costs with regard to sick-listed temporary agency workers are the sickness benefit costs paid by the SSA. However, this does not apply to unemployed workers. These workers have no work(place), i.e. there is no productivity. As a consequence, being sick-listed does not result in a productivity loss. Another important fact is that an unemployed worker receives an unemployment benefit. After reporting sick with acceptance of the sickness benefit claim by the SSA, the sick-listed unemployed worker receives a sickness benefit instead of an unemployment benefit. However, the amount of these benefits can differ as this is established using different income conditions. As a result, the sickness benefit can be more than the unemployment benefit. From this perspective, the additional benefit costs are considered indirect costs in this study. Data on paid benefits are collected from the SSA database after the one-year follow-up. Cost-benefit evaluation of the new RTW program is part of this study and will be discussed below.

An overview of the outcome measures and the measurement instruments used, including a time path for all measurements, is presented in table 2.

**Table 2 T2:** Overview of measurements and time path

Measurement	Time path				
	**Baseline**	**3 months**	**6 months**	**9 months**	**12 months**

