### Statistical analyses

All statistical analyses will be performed at worker's level and according to the intention-to-treat principle, i.e. participants will remain in the group (intervention group or control group) to which they were allocated after randomisation at baseline. To check the success of the randomization procedure descriptive statistics will be used, comparing the baseline measurements of both groups. If necessary, analyses will be adjusted for prognostic dissimilarities. To asses the presence of bias due to protocol deviations, the results of the intention-to-treat-analyses will be compared to per-protocol analyses, including only those participants who were treated according to the intervention protocol.

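### The plan permits adjusting the effect analysis for co-interventions recorded after randomisation and does not confine this to an exploratory model; if their use depends on allocation, the adjusted estimate is not the total effect of assignment

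*Protocol article*

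**What the plan says.** Under Co-interventions and compliance, the protocol article accepts that in this pragmatic trial "it is not possible to avoid co-interventions during the intervention period". It then says that "both the intervention group and the control group are asked about co-interventions in each follow-up questionnaire", and closes with the provision at issue: "If necessary, we can adjust for co-interventions in the multivariate analysis". The outcome and the model are not named.

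Under Statistical analyses, the general rule is "All statistical analyses will be performed at worker's level and according to the intention-to-treat principle", which the article explains as participants staying in the group to which they were allocated. Two further provisions follow. One concerns baseline differences between the groups: "If necessary, analyses will be adjusted for prognostic dissimilarities". The other is a check for protocol deviations: "the results of the intention-to-treat-analyses will be compared to per-protocol analyses". The Effect evaluation subsection names Kaplan-Meier and Cox methods for the first benefit period, a general linear model for total benefit days, and longitudinal random coefficient models for secondary outcomes. The only covariate adjustment it mentions is for dissimilarities at baseline. Co-interventions appear in neither place.

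**The concern.** A covariate recorded during follow-up can be a consequence of allocation. Three parts of the article make this plausible here.

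- **Preparation of implementation:** the program ends in a plan that assigns someone to carry out each chosen solution. Other care could be one of those solutions, or could be replaced by one.
- **Blinding:** the professionals who may guide workers in both arms know the allocation, so the other care they arrange can differ by arm.
- **The Dutch Social Security System:** the SSA's occupational health care stops when the sickness benefit ends. The end of the benefit is the primary event, so a worker who leaves benefit early has less time to receive such care. A covariate for whether a worker ever had a co-intervention is then partly a result of the outcome.

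The effect of a pragmatic program includes the care it sets in motion or makes unnecessary. Adjusting for that care can remove part of a real effect. If an unmeasured factor such as severity drives both co-intervention use and slow recovery, adjustment can also produce an apparent effect where none exists. A difference in use between arms is the likeliest reason to think adjustment necessary, and that is the case in which adjustment does harm.

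**Working it through.** **The plan's own figures.** For HR 2.0, two-sided alpha 0.05 and power 0.80, Schoenfeld's formula gives events = 4 × (1.960 + 0.842)² / (ln 2)² = 65.3, so 66. With 2/3 of participants having the event, N = 66 / (2/3) = 99, against 100 stated. Then 100 × 1.1 = 110, and 110 × [1 + (10 − 1) × 0.05] = 159.5, so 160. These match the Sample size section. The present point does not affect them.

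**Inputs for size.** The documents give no rates or effects for co-interventions. All such inputs below are assumptions. The setting is a Cox model with one-year censoring, using very large samples so that the results show bias and not chance.

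| Assumed situation | HR without co-intervention term | HR with it |
|---|---|---|
| (a) Program raises use from 30% to 70%; direct HR 1.5; co-intervention HR 2.0 | 1.93 | 1.50 |
| (b) Effect only through co-interventions: use 20% to 80%; co-intervention HR 2.5 | 1.72 | 1.02 |
| (c1) No effect; unmeasured severity raises use and slows recovery; program raises use from 30% to 60% at average severity | 0.99 | 1.14 |
| (c2) As c1, but program lowers use from 60% to 30% | 1.01 | 0.87 |
| (d) Use unrelated to allocation and severity; program HR 2.0 | 1.97 | 1.99 |

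The baseline hazard is 0.75 per year and 54% to 71% of participants have the event. In (c1) and (c2) one standard deviation of severity changes the log hazard by −0.8 and the log odds of use by +1.0.

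**Hand check of (a) and (b).** At the start of follow-up the total HR is the direct HR × [1 + p1 × (HRc − 1)] / [1 + p0 × (HRc − 1)], where p1 and p0 are use by arm and HRc is the co-intervention HR.

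- (a): 1.5 × 1.7 / 1.3 = 1.96.
- (b): 2.2 / 1.3 = 1.69.

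Both are close to the simulated values without the term. With the term, the model returns the direct effect (1.50, and about 1), which answers a different question.

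**Use that depends on time on benefit.** Suppose the co-intervention has no effect and can be received only while benefit runs, the program has no effect, and about 2/3 of benefits end in the year. With use of 53% in the program arm and 29% in the control arm, the HR goes from 0.99 to 1.34 after adjustment. With the arms reversed it goes from 1.00 to 0.74. Such proportions arise from constant uptake rates r of about 1.5 and 0.6 per year. With end-of-benefit hazard h = ln 3 = 1.10, use = r/(r + h) × [1 − exp(−(r + h))], which gives 0.53 and 0.29. With equal uptake rates in both arms, adjustment changes little (0.99 to 1.01 under no effect; 2.07 to 2.00 under an effect).

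**What attenuation would mean.** With 66 events, power is Φ(√66 / 2 × ln HR − 1.96). This gives 0.80 at HR 2.0. At HR 1.5 it is Φ(4.06 × 0.405 − 1.96) = Φ(−0.31) = 0.38. A shift of the size in (a) could decide the trial's conclusion if the adjusted result were taken as the main one.

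**The case against.** The strongest reply is that the sentence only reserves an option. The sections that define the analysis specify intention-to-treat and baseline adjustment and do not mention co-interventions, so they can be read as fixing the main analysis, with the co-intervention model as a supplement. This limits the point: the documents do not show that the primary hazard ratio will be adjusted in this way. It does not remove the point, because nothing says the option is supplementary, and the per-protocol comparison is a different analysis.

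A reader might infer that the adjusted estimate must be biased. The documents do not support that. The harm depends on use being related to allocation, which the article makes plausible but does not state; case (d) shows almost no change. The cost section lists "interventions aimed at health promotion, e.g. physical therapy (graded activity) and/or psychological help" among the care the SSA pays for, but it does not call these items co-interventions or say that the program triggers them.

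A reader might also infer that an adjusted analysis ceases to be intention-to-treat. By the article's definition it does not, since everyone stays in the allocated group. What changes is the quantity estimated.

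Finally, one might fault the undefined trigger as a choice left open until the data are seen. Trigger rules can reasonably sit in a statistical analysis plan that is not shown, and the Blinding section says the researcher will analyse the data blinded. The point here is the kind of variable the plan admits, which the article states outright.

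**Conclusion.** The concern holds in conditional form. The article expressly permits adjustment for variables recorded after randomisation and does not restrict that permission to an exploratory analysis. If the program changes co-intervention use, or if use depends on time spent on benefit in a way that differs by arm, the adjusted hazard ratio is not the total effect of assignment. The error can go either way.

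Its size cannot be taken from the documents. Under the assumptions shown, a total HR of 1.93 becomes 1.50, and a true HR of 1.0 becomes 0.87 or 1.14. Where care can be received only while benefit runs, the null value moves as far as 0.74 or 1.34. If use is unrelated to allocation, the change is negligible. The main analysis as written in the statistical section is sound; the permission elsewhere in the article needs to be restricted.

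**What to change.** Replace the closing sentence of Co-interventions and compliance with a statement along these lines:

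- The main effect models (Cox, general linear and longitudinal) adjust only for baseline or stratification variables.
- Co-interventions are reported descriptively by arm.
- Any model that includes co-interventions is labelled exploratory, states its assumptions, and does not replace the main estimate.

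The Effect evaluation subsection should carry the same rule. An outright ban on such models is not needed. The cost is a few lines of text, with no change to data collection, follow-up or sample size.
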